#### Statistical analysis

##### Sample size

ᅟ

### Phase I, safety evaluation

Only acute GU and/or GI grade 3 or higher toxicity will be considered for the safety evaluation. Three patients will be treated and evaluated for toxicity at 3 months. If the first 3 patients undergo any grade ≥ 3 toxicity or if 2 patients under go grade 4 toxicity, the trial will stop.

Otherwise, 3 additional patients will be recruited and treated. If 2/6 patients or fewer present with grade 3 AE, the trial will go on phase II and include 39 additional patients. Regarding these 6 patients, if one or more present with grade 4 toxicity, a meeting of the *Data Safety and Monitoring Board* (DSMB) will be carried on.

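### The phase I stop/go rule is ambiguous and uses two event definitions, so identical toxicity data can stop the trial under one reading and open phase II under another

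*Protocol article*

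**What the plan says.** The rule is one short paragraph in the protocol article, under Sample size, Phase I, safety evaluation. In order, it says:

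- Event: "Only acute GU and/or GI grade 3 or higher toxicity will be considered for the safety evaluation".
- First look: "Three patients will be treated and evaluated for toxicity at 3 months".
- Stop: "If the first 3 patients undergo any grade" ≥ 3 "toxicity or if 2 patients under go grade 4 toxicity, the trial will stop".
- If that does not apply, three more patients are treated.
- Go: "If 2/6 patients or fewer present with grade 3 AE, the trial will go on phase II", with 39 further patients.
- DSMB: for the six patients, "if one or more present with grade 4 toxicity, a meeting of the" DSMB is held. No outcome of that meeting is given.

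The section on the primary endpoint of the phase I trial also defines the safety event as grade ≥ 3 acute GU and GI events in the first three months.

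**The concern.** This paragraph is the only gate stated before 39 more patients are treated, and the whole dose is given in one fraction, so a decision to go on cannot be undone for patients already treated. A gate of this kind should lead anyone holding the same data to the same action. Three features prevent that:

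- **(a) Who must have the event.** The first stop limb does not say whether one patient with grade ≥ 3 is enough or whether all three must have it.
- **(b) Denominator of the grade 4 limb.** It says two patients without saying two of how many. It could apply to the first three or to all six.
- **(c) Event counted at six patients.** The go rule counts grade 3, while the paragraph's opening sentence counts grade 3 or higher. Read literally, grade 4 and grade 5 events do not count against going on. The text also gives no action when three or more of six have grade 3.

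**Working it through.** **Inputs from the document.** Cohorts of 3 and 3; stop, go and DSMB thresholds as listed above. The paragraph's sample size agrees with the phase II section: 6 + 39 = 45. No operating characteristics are stated for the phase I rule, so there is no further figure to reproduce.

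**Assumptions.** Patients are independent. The article gives no expected acute toxicity rate for phase I, so the true per-patient rate *p* is set at 5%, 10%, 20% and 30%.

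**Step 1: map the outcomes, grade 3 events only.** Where a reading stops after three patients, the next three are never treated; the second column then only identifies the data on which the other reading acts.

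| Grade 3 in first three | Grade 3 in next three | *At least one* | *All three* |
|---|---|---|---|
| 0 | 0, 1 or 2 | phase II | phase II |
| 0 | 3 | no action stated | no action stated |
| 1 | 0 or 1 | stop | phase II |
| 1 | 2 or 3 | stop | no action stated |
| 2 | 0 | stop | phase II |
| 2 | 1, 2 or 3 | stop | no action stated |
| 3 | not treated | stop | stop |

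**Step 2: does the grade 4 limb do anything at the first look?** With each of three patients at grade < 3, 3 or 4 there are 3³ = 27 patterns. Under *at least one*, the limb adds 0 stopping patterns, because any grade 4 has already stopped the trial. Under *all three* it adds 3 (two grade 4 and one below grade 3, in three orders).

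**Step 3: size of the difference, grade 3 events only.**

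- *At least one*: stop at first look = 1 − (1−p)³; reach phase II = (1−p)³ × (1−p³).
- *All three*: stop at first look = p³; reach phase II = P(Bin(6,p) ≤ 2) = (1−p)⁶ + 6p(1−p)⁵ + 15p²(1−p)⁴.
- Example at p = 0.20: 0.512 × 0.992 = 0.508, against 0.2621 + 0.3932 + 0.2458 = 0.901.

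| True rate | 5% | 10% | 20% | 30% |
|---|---|---|---|---|
| Stop at first look, *at least one* | 14.3% | 27.1% | 48.8% | 65.7% |
| Stop at first look, *all three* | 0.01% | 0.1% | 0.8% | 2.7% |
| Reach phase II, *at least one* | 85.7% | 72.8% | 50.8% | 33.4% |
| Reach phase II, *all three* | 99.8% | 98.4% | 90.1% | 74.4% |
| Stop on one reading, phase II on the other | 14.1% | 25.6% | 39.3% | 41.1% |

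The chance of landing where no action is stated is the remainder, 1 − stop − go. Under *all three* at 20% it is 1 − 0.008 − 0.901 = 9.1%; at 30% it is 1 − 0.027 − 0.744 = 22.9%. Under *at least one* it is (1−p)³p³, which is 0.4% and 0.9%.

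**Step 4: scope of the grade 4 limb.** Take no grade ≥ 3 in the first three, then two grade 4 and no grade 3 in patients 4 to 6. If the limb covers all six, these data meet the stop limb (two grade 4), the go rule (0 of 6 with grade 3) and the DSMB trigger (at least one grade 4) together. If it covers only the first three, only the go rule and the DSMB trigger apply.

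**Step 5: event counted by the go rule.** Take the *all three* reading with the grade 4 limb confined to the first three. One grade 4 in the first three and two in the next three, with no grade 3, passes the go rule as written; the only other consequence stated is the DSMB meeting. Enumerating all 3⁶ = 729 patterns, with the DSMB meeting not counted as a stop, gives the chance of meeting the go rule:

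| Assumed grade 3 / grade 4 rate | Go rule counts grade 3 only | Go rule counts grade ≥ 3 |
|---|---|---|
| 8% / 2%, *all three* | 99.0% | 98.3% |
| 20% / 10%, *all three* | 86.8% | 73.7% |
| 8% / 2%, *at least one* | 72.9% | 72.8% |
| 20% / 10%, *at least one* | 34.0% | 33.4% |

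The event definition therefore matters mainly under *all three*, and when grade 4 events are not rare.

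**The case against.** The strongest reply is that the paragraph is sequential. The second cohort is reached only if the stop rule is not met, so under either reading, with the stop sentence applied to the first three patients, no data pattern both stops the trial and sends it on. The *all three* reading is coherent and gives the grade 4 limb a function; *at least one* is coherent too, with a limb that is merely superfluous. The opening sentence could also be taken to carry grade 3 or higher through to the go rule. All of this is right about each reading alone. It does not settle which reading applies, and the actions differ.

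Four stronger inferences are tempting and not supported:

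- **That the sentences contradict each other outright**, for instance because one grade 4 in the first three would both stop the trial and only call a DSMB meeting. Under *at least one* the trial has then stopped, and the group of six never exists. A true stop-and-go clash needs the grade 4 limb read over all six (Step 4).
- **That the rule has no definable operating characteristics.** Each reading has them; they are computed above.
- **That different sites would decide differently.** Nothing in the article has sites apply this trial-level rule.
- **That the threshold is out of line with the grade 3 rates cited in the Background.** The SBRT rates there are for late toxicity, mostly after five fractions; phase I counts acute events after one.

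A last reply is that the full protocol may hold a clearer rule. It may, but the article prints thresholds and actions, and the defect lies in what it prints.

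**Conclusion.** The point stands as an ambiguous and internally inconsistent decision rule, and it needs to be settled because it is the only stated gate to phase II. The choice of reading moves the chance of reaching phase II by about 14, 26, 39 and 41 percentage points at true grade 3 rates of 5%, 10%, 20% and 30%. Those figures rest on assumed rates, independent patients and no grade 4 events. The open scope of the grade 4 limb, the grade 3 wording of the go rule and the missing action at three or more of six are smaller defects of the same kind. The document does not allow a reader to say which rule was intended, and this review takes no position on it.

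**What to change.** The sponsor and the DSMB should replace the paragraph with one table that gives, after 3 and after 6 patients, a single action for every combination of the number of patients with grade ≥ 3 and the number with grade ≥ 4 events. It should:

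- use the same event definition at both looks, with grade 5 placed explicitly;
- give every count its denominator (first three or all six);
- include the cells with three or more of six;
- where a cell calls for a DSMB meeting, state whether recruitment waits and which decisions the DSMB can take.

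The probability of going on at a few true rates could be printed beside the table or left to the analysis plan; it is not needed to cure the defect. If the full protocol already has one unambiguous rule, bringing the published text into line with it is enough. The cost is one table and DSMB sign-off, with no extra patients and no change to the total of 45.

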### Phase II, efficacy evaluation

Based on published SBRT results on 5 fraction-trials and on one series of HDR-BT with 19 Gy single shot, a 3-yearsbRFS of 96% may be expected. Assuming this hypothesis and an expected dropout rate of 10%, 45 patients (including the 6 included in the phase I study) will allow evaluating 3-year bRFS with a 97.5% lower one-sided confidence interval and a width of the interval of 0.06 (upper bound = 90%).

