#### Phase II- statistical analysis of the primary endpoint

Efficacy analyses will be performed on an intention to treat basis (i.e., involving those patients following the major inclusion criteria and repeated one per protocol set). The primary endpoint is 3-years bRFS. bRFS, and its 97.5% one-sided confidence interval (CI), will be determined using the *Kaplan Meier* method. If the expected value of 96% isn’t included in this interval, the efficacy of the experimental treatment will be questioned.

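### The phase II precision statement (width 0.06, limit 90%) rests on a large-sample formula with about 1.6 expected failures; suitable methods put the lower limit near 83–85%

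*Protocol article*

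**What the plan says.** The phase II sample-size paragraph of the protocol article (Statistical analysis, Sample size, Phase II, efficacy evaluation) states that "a 3-yearsbRFS of 96% may be expected". It then assumes "an expected dropout rate of 10%, 45 patients (including the 6 included in the phase I study" and describes the resulting precision as a "97.5% lower one-sided confidence interval and a width of the interval of 0.06", with 90% given in brackets and labelled the upper bound. It names no formula, and no power or test calculation stands beside it.

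The section on the primary endpoint analysis says that the one-sided 97.5% interval for 3-year bRFS "will be determined using the *Kaplan Meier* method", without naming a transformation. Its decision rule is: "If the expected value of 96% isn’t included in this interval, the efficacy of the experimental treatment will be questioned".

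**The concern.** The expected proportion is close to 1 and the sample is small, so very few failures will determine the interval. A symmetric normal interval performs badly in that setting. If the 0.06 comes from such an interval, the design does not have the precision printed for it. The figure is the only statistical justification given for the phase II size, so a reader planning a later trial from this one would expect a much tighter lower limit than 45 patients can usually give.

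The label adds confusion: 0.96 − 0.06 = 0.90 is the lower end of the interval, yet it is printed as an upper bound.

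**Working it through.** **Inputs**, all from the phase II sample-size paragraph: p = 0.96; 45 patients with 10% dropout, so 45 × 0.9 = 40.5, or 40 to 41 evaluable; one-sided 97.5%, so z = 1.96; width w = 0.06.

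**Step 1: reproduce the plan's figure.** With the plain normal formula, n = p(1 − p)(z/w)² = 0.96 × 0.04 × (1.96/0.06)² = 40.98. Allowing for dropout gives 40.98 × 1.1 = 45.1 or 40.98/0.9 = 45.5, in line with 45. In the other direction, 1.96 × sqrt(0.96 × 0.04/n) is 0.0600 at n = 41 (limit 0.900) and 0.0607 at n = 40 (limit 0.899). One-sided 95% (29 evaluable) and two-sided 97.5% (54 evaluable) do not lead to 45.

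**Step 2: expected failures.** 40 × 0.04 = 1.6, and 41 × 0.04 = 1.64.

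**Step 3: lower limits at an estimate of 0.96 by methods suited to a proportion near 1**, with no censoring before 3 years.

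- Wilson: [p + z²/2n − z × sqrt(p(1 − p)/n + z²/4n²)]/(1 + z²/n). At n = 40 this is (1.0080 − 0.0774)/1.0960 = 0.849.
- Exact (Clopper-Pearson): the 2.5% quantile of Beta(np, n − np + 1). At n = 40 this is 0.845.
- Log-log with Greenwood variance: p raised to exp(z × s), with s = sqrt((1 − p)/(pn))/|ln p|. At n = 40, s = 0.03227/0.04082 = 0.791, the exponent is 4.71, and the limit is 0.825.

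| n | Plain | Wilson | Exact | Log-log |
|---|---|---|---|---|
| 40 | 0.899 | 0.849 | 0.845 | 0.825 |
| 41 | 0.900 | 0.851 | 0.847 | 0.828 |
| 45 (no dropout) | 0.903 | 0.858 | 0.855 | 0.839 |

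The widths at n = 40 are 0.96 − 0.849 = 0.111, 0.96 − 0.845 = 0.115 and 0.96 − 0.825 = 0.135, against the stated 0.06.

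**Step 4: limits by whole failures, n = 40, true rate 96%.**

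| Failures | Probability | Exact | Wilson | Log-log |
|---|---|---|---|---|
| 0 | 0.195 | 0.912 | 0.912 | undefined |
| 1 | 0.326 | 0.868 | 0.871 | 0.835 |
| 2 | 0.265 | 0.831 | 0.835 | 0.815 |
| 3 | 0.140 | 0.796 | 0.801 | 0.785 |

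The expected exact limit is 0.848. An exact or Wilson limit of at least 0.90 occurs only with no failures: 0.96^40 = 0.195 (0.96^45 = 0.159 if all 45 are evaluable). Three or more failures have probability 1 − 0.1954 − 0.3256 − 0.2646 = 0.214.

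**Step 5: scale.** A limit of 0.90 at an estimate of 0.96 would need about 97 (Wilson), 99 (exact) or 107 (log-log) evaluable patients.

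**The case against.** The strongest reply is that the arithmetic is right. It is: the fault lies in the choice of approximation, not in a slip. That does not rescue the printed precision, because the formula is being used where it is unreliable.

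Several stronger readings are tempting and should be resisted.

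- *That the protocol claims to rule out a bRFS below 90%.* It does not. It states a width, and its only decision rule compares the interval with 96%. The 90% is not a threshold anywhere, and correcting the lower limit leaves that rule as it stands.
- *That only the plain formula gives 0.06.* A log-transformed normal interval also gives about 0.90 (0.901 at n = 40, 0.902 at n = 41), but it is a large-sample approximation too. Less conservative methods give 0.864 (Jeffreys) and 0.878 (arcsine) at n = 40. The size of the correction therefore depends on the method, though these two also stay below 0.90.
- *That poor coverage of the plain limit argues for log-log.* At a true 96% and n = 40 the plain limit covers only 80.5% of the time, but the whole shortfall is the zero-failure case (19.5%), where log-log is undefined as well. Only an exact fallback for no events changes that figure.
- *That the analysis section is deficient because it names no transformation for the Kaplan-Meier interval.* A protocol article may leave that detail to the statistical analysis plan, and nothing in the text says that the plain interval will be used.

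A last objection is that dropouts contribute partial follow-up. This places the result between the rows for 40 and 45 patients, where the Wilson, exact and log-log limits are still at most 0.858.

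**Conclusion.** The concern holds as a wrong stated precision in the sample-size paragraph. With about 40 evaluable patients and a 3-year bRFS of 96%, the one-sided 97.5% lower limit is about 0.85 by exact or Wilson methods and about 0.83 by log-log. The width is 0.11 to 0.135, not 0.06, and an exact or Wilson limit of 90% or more would be reached about one time in five. The figure of 90% is a lower limit and is mislabelled.

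This rests on two assumptions: dropouts give no information, and there is no other censoring before 3 years. Relaxing the first up to full follow-up of all 45 does not change the conclusion. The finding does not show that 45 patients is the wrong number, because the protocol ties no decision to 90%.

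**What to change.** Keep 45 patients. Restate the precision with one method, used for both planning and analysis, and call the figure a lower limit. For the exact method the text could read:

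> With about 40 evaluable patients and a true 3-year bRFS of 96%, the expected one-sided 97.5% lower limit is about 85% (width about 0.11): 91%, 87%, 83% and 80% with 0, 1, 2 and 3 failures; three or more failures have probability about 21%.

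If the analysis will use log-log Kaplan-Meier limits, quote those instead: about 83% at an estimate of 96%, and 0.835 and 0.815 with one and two failures, with an exact limit if there are no events. Exact planning figures should not be paired with a log-log analysis.

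The cost is a rewritten sentence or two and a line naming the interval. No patients are added. The downside is that the stated precision becomes less favourable.

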### Data analysis

Data description will be performed using the mean, standard deviation, median, and range for quantitative variables and the percentage for qualitative ones.

#### Phase I

Safety analyses shall be performed on the safety-evaluable population, defined as all subjects treated with the single shot SBRT. Toxicity and grade will be described at each follow-up visit according to the specificity of every assessed endpoint, including the number and fraction of patients with at least one AE.

#### Phase II- statistical analysis of the primary endpoint

Efficacy analyses will be performed on an intention to treat basis (i.e., involving those patients following the major inclusion criteria and repeated one per protocol set). The primary endpoint is 3-years bRFS. bRFS, and its 97.5% one-sided confidence interval (CI), will be determined using the *Kaplan Meier* method. If the expected value of 96% isn’t included in this interval, the efficacy of the experimental treatment will be questioned.

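### The phase II rule checks whether 96% lies inside a lower one-sided interval, so a poor 3-year bRFS can never cause efficacy to be questioned

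*Protocol article*

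**What the plan says.** Under Sample size, *Phase II, efficacy evaluation*, the protocol article states that "a 3-yearsbRFS of 96% may be expected". It allows for "an expected dropout rate of 10" per cent and takes "45 patients (including the 6 included in the phase I study"). The precision aim is to estimate 3-year bRFS "with a 97.5% lower one-sided confidence interval and a width of the interval of 0.06 (upper bound = 90" per cent).

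Under Data analysis, *Phase II- statistical analysis of the primary endpoint*, it says "The primary endpoint is 3-years bRFS", to be estimated by Kaplan-Meier with a one-sided 97.5% confidence interval whose direction is not repeated. The decision sentence follows: "If the expected value of 96% isn’t included in this interval, the efficacy of the experimental treatment will be questioned". The article gives no other efficacy criterion for phase II.

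**The concern.** The decision sentence is meant to raise a flag when results fall short of 96%. The interval defined in the sample-size section is bounded only from below, and such an interval cannot rule out a value for being too high. Poor results push its lower limit down and leave 96% inside. The one stated criterion for the primary efficacy endpoint would then be unable to give an unfavourable signal, however many patients relapse.

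Two further weaknesses come with it. The 90% limit is labelled an upper bound although it lies below the estimate, so the reader cannot be sure which side was meant. And 90%, the only benchmark below 96% in the design, is used for planning and then plays no part in any decision.

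**Working it through.** **Inputs** (protocol article, Sample size and Data analysis sections): expected bRFS 0.96; width 0.06; one-sided 97.5%, so z = 1.96; dropout 10%; N = 45. The calculations treat 3-year bRFS as an uncensored binomial proportion.

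**1. Reproducing the plan's N and the direction of its interval.**
n = z² × p(1 − p) / width² = 1.96² × 0.96 × 0.04 / 0.06² = 40.98, so 41 evaluable.
Dropout: 40.98 / 0.9 = 45.5, or 40.98 × 1.1 = 45.1. The stated 45 is reproduced to within a patient or so. A one-sided 95% level would give 29 evaluable (33 with dropout), which does not match.
The limit is 0.96 − 0.06 = 0.90, below the estimate. The figures therefore support a lower limit, and the label is the error.

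**2. The rule as written.** The interval is [L, 100%], and 96% is outside it only if L > 96%.
With zero relapses the exact limit is L = 0.025^(1/n):
- n = 40: 91.2%
- n = 41: 91.4%
- n = 45: 92.1%

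Every relapse lowers L. At n = 41, exact L is 87.1% with 1 relapse, 73.8% with 5 (observed 87.8%) and 59.7% with 10 (observed 75.6%). In each case 96% is inside. For L to exceed 96% with no relapses, n must exceed ln(0.025)/ln(0.96), that is, at least 91 patients.

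**3. The rule if an upper limit U was meant.** Efficacy is questioned if U < 96%.
- Exact, n = 40: 4 relapses give U = 97.2%, 5 give 95.8%. Trigger: 5.
- Exact, n = 41: 5 relapses give U = 95.9%. Trigger: 5.
- Exact, n = 45: 5 relapses give U = 96.3%, 6 give 94.9%. Trigger: 6.
- Log-log: trigger 5 at n = 40, 41 and 45.
- Plain (Wald/Greenwood), n = 40: 6 relapses give U = 96.1%, 7 give 94.3%. Trigger: 7.

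Probability that efficacy is **not** questioned at n = 40, i.e. P(relapses ≤ trigger − 1):

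| True 3-year bRFS | Exact (trigger 5) | Plain (trigger 7) |
|---|---|---|
| 90% | 63% | 90% |
| 85% | 26% | 61% |
| 81% | 10% | 34% |

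If the truth is 96%, the exact flag is raised wrongly 2.1% of the time.

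**4. The lower limit against the 90% planning value.** With exact limits at n = 40, zero relapses give L = 91.2% and one relapse gives 86.8%. Only zero relapses clear 90%. If the truth is 96%, that has probability 0.96^40 = 20%.

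**The case against.** The strongest reply is that the analysis section says only one-sided, and that a sentence meant to question efficacy when results disappoint makes sense only with an upper limit. On that view the defect is a mislabelled interval, not a rule that anyone intended to be inert. As an account of intent this is plausible. It does not remove the problem: the sample-size wording and arithmetic both define a lower interval, no other interval is defined, and an analyst who follows the text gets a rule that poor results cannot trigger.

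It is also fair to say that the trial is sized for precision, not for a test, and that N is right for that purpose. That stands, and the sample size is not criticised here.

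Several stronger readings are tempting but not supported:
- A reader might infer that including 96% will be read as proof of efficacy. The article says only when efficacy will be questioned and is silent on the other outcome.
- A reader might infer that a phase III go/no-go hangs on this rule. The Abstract and Discussion say that results, if positive, may help to design later trials, and the Background says they will help determine the design. None of them ties a positive result to the 96% rule.
- A reader might infer that, with an upper limit, inferior treatments would usually escape the flag. With exact limits that holds at a true 90%, but not at 85% or 81%.
- A reader might note that a perfect result would be questioned. That arises only with the plain interval at zero relapses, where the variance collapses to zero, and the article names no interval type.

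**Conclusion.** The concern holds. Under the interval that the protocol article defines, a poor 3-year bRFS can never trigger the decision rule, and with exact limits at 40 to 45 evaluable patients no result can. This follows from the shape of the interval and does not depend on the method of computing L.

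Under the alternative upper-limit reading the flag works but is insensitive near the 90% planning value, where a treatment goes unquestioned in 63% (exact) to 90% (plain) of trials at n = 40. It becomes more dependable as the truth falls, above all with exact limits. These probabilities assume complete 3-year follow-up of the evaluable patients; censoring would change them, and the trigger count shifts with n and with the interval method.

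The rule must be corrected, because it is the only efficacy criterion stated for the primary endpoint and gives the wrong answer if followed.

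**What to change.** 1. In the sample-size section, change the label on the 90% limit from upper to lower bound.
2. In the analysis section, replace the decision sentence with: efficacy is questioned if the upper 97.5% confidence limit of 3-year bRFS is below 96%. Name the interval method (for example log-log or exact), the relapse count that triggers the flag at the expected number evaluable, and the probability of triggering it over a range of true rates.
3. State that an untriggered flag is not in itself evidence of efficacy.
4. Report the lower 97.5% limit alongside and compare it with the 90% planning value. Disclose that with exact limits at n = 40 it exceeds 90% only with zero relapses, a 20% chance if the truth is 96%.

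Any other minimum acceptable rate has no basis in the article and would turn a precision design into a test; that choice is for the sponsor to justify.

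Cost: wording and a short table of operating characteristics, with no extra patients. The drawback is that the trial's stated ability to show efficacy will look less favourable.
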